### Child Weight-Related Behaviors

#### Dietary Intake and Diet Quality

Primary caregivers report their child’s dietary intake for 1 day using the web-based Automated Self-Administered 24-hour Dietary Assessment Tool (ASA24)-Canada. ASA24 includes multiple prompts for participants to facilitate accurate data entry. A validity study that compared parent reports to children’s true diet intake among 40 parent-child dyads found that parents could accurately report what young children ate and drank [60]. ASA24-Canada analyzes the dietary data using the Canadian Nutrient File and a Health Canada recipe database along with the United States Food and Nutrient Database for Dietary Studies and the Food Patterns Equivalents Database. These databases enable ASA24-Canada to output a summary of the food descriptions, energy and nutrient intakes, and United States Department of Agriculture Food Pattern components. This information will be used to examine children’s intake based on evidence that stress is associated with a higher intake of fast food [61,62], high-fat and high-sugar foods [13], and lower intake of fruit and vegetables [13].

#### Eating Behavior

Further, 4 eating behaviors that are most consistently associated with increased obesity risk in children (enjoyment of food [4 items], food responsiveness [5 items], emotional overeating [4 items], and satiety responsiveness [5 items]) [3,63,64] are assessed using the Children’s Eating Behavior Questionnaire [65]. Parents report their children’s eating behavior for each of these behaviors, for example, “my child eats more when anxious.” Response options for each item include “never” (1), “rarely” (2), “sometimes” (3), “often” (4), and “always” (5). After reverse coding relevant items, a mean score will be calculated for eating behavior with higher scores reflecting higher endorsement of these behaviors. The Children’s Eating Behavior Questionnaire subscales have been shown to have good internal consistency (Cronbach α ranging from 0.72 to 0.91) when tested among a sample of families with young children [65].

#### Physical Activity, Sedentary Behavior, Sleep, and Screen Time

A lightweight activity monitor (wGT3x-BT; Actigraph; 100 Hz) with idle sleep mode enabled to preserve battery life, is fixed to a soft strap and placed on the child’s right hip for 7 consecutive days, 24 hours/day, and the monitors are returned via prepaid mail or picked up from participant’s homes. To aid with compliance, caregivers are provided with a link to an animated video to share with their child about the activity monitor and why they are being asked to wear it. Caregivers complete a log sheet to track monitor wear-time, including times that the device is removed (ie, bathing) in addition to their child’s sleep and wake times. Using validated age-appropriate cut-point values [66], data collected from the monitors will then be used to quantify physical activity, that is, total physical activity and moderate to vigorous physical activity, total sedentary time [67], and total sleep [68,69].

Primary caregivers report child screen time defined as “any time that is spent on screens such as televisions, cell phones, iPads or tablets and video games” on a typical weekday and weekend day over the past week [70]. Weekday and weekend day values will be summed and averaged to calculate the average daily screen time.

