## Introduction

Chronic stress is increasingly recognized as an important risk factor in the development of obesity [1]. Among children aged as young as 2-6 years, exposure to chronic stress, including parental divorce, parental depression, and household chaos has been associated with higher weight status and excess weight gain over time [2-4]. The COVID-19 pandemic fundamentally disrupted life for families and has been a key source of chronic stress for young children [5,6] and their parents [7].

While research suggests chronic stress is linked to excess weight gain in children, the biological or behavioral mechanisms are poorly understood [8]. Biologically, a central aspect of the stress response is the activation of the hypothalamic-pituitary-adrenal axis, leading to increased circulating cortisol levels [9]. Prolonged elevation of cortisol, a glucocorticoid, leads to increased adiposity, particularly abdominal adiposity, as well as increased appetite and preferences for high-fat and high-sugar foods [9]. Few studies have examined the association between cortisol and obesity among young children and most of this research has been cross-sectional [10-12]. Biological stress could be implicated in weight gain through complex pathways that develop over time; thus, longitudinal research is needed to elucidate the direction of these pathways [8]. Putative behavioral mechanisms linking stress with excess weight gain include consumption of energy-dense foods [13], eating for comfort [14], low physical activity [15], high screen time [16], and poor sleep [17]. However, research examining these mechanisms over time is sparse, particularly among young children [8]. Understanding these behavioral mechanisms, including the relative contributions of weight-related behaviors linking family stress and excess weight gain in children, can help inform behavioral targets for obesity interventions for young children who experience stress in the home.

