An incremental model-building approach similar to the recommended approach by Curran et al [80] will be used to test this study’s objectives. The first component in the model-building approach is the LGM of the trajectories across time for the variables’ chronic stressors (explanatory variable), child cortisol and child behavior (mediator variables), and child adiposity (outcome variable). Each variable has its own trajectory and includes an intercept (I), which refers to a baseline value, and a slope (S), which refers to change over time. Of particular importance is that individual child variation in these I and S parameters will be modeled. If any of these components are found to be not statistically significant, they are removed from the model. Typically, the I means and variances are significantly different from 0, but the S means may or may not depict significant linear change. The second component consists of the auto-regressive associations (ie, T2 regressed on T1, and T3 on T2) capturing the rank-order stability of the variables across the 3 time points (eg, the relationship between cortisol at T1 and T2). The third component typically consists of cross-lagged paths or other hypothesized paths between the variables, accounting for growth factors, and stability factors. In this study, this component will consist of the longitudinal mediation paths (ie, from explanatory variable at T1 to mediator at T2, to outcome at T3). The hypothesized model includes 2 partial mediators of the relation between stressors and child adiposity: child cortisol and behaviors. To test mediation, a direct path from stressors at T1 and child adiposity at T3 is also included. A correlational path between the residualized mediators is also included to model any leftover covariance between them. The fourth component will assess the moderation of the mediated paths. For example, to test the hypothesis that the cortisol mediation may differ across the sex of the children, we can use a multiple groups SEM approach that compares the effect size of mediation across male and female children.

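### As written, daily screen time is an unweighted mean of one weekday and one weekend-day value, so weekends count 1/2 instead of 2/7; the fix is one line and the likely effect on mediation paths is small

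*Protocol article*

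**What the plan says.** The protocol article, under Physical Activity, Sedentary Behavior, Sleep, and Screen Time, has the primary caregiver report the child's screen time "on a typical weekday and weekend day over the past week". That yields two numbers per child per wave. The derivation follows: "Weekday and weekend day values will be summed and averaged to calculate the average daily screen time". No weights are given there or anywhere else in the article.

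Screen time falls under the heading Child Weight-Related Behaviors, and the Introduction names high screen time among the putative behavioural mechanisms linking stress to excess weight gain. Data Analyses lists "child cortisol and child behavior (mediator variables") among the variables whose trajectories are modelled. Data Collection says that weight-related behaviours are assessed at baseline and at the 1- and 2-year follow-ups, so the rule applies three times per child.

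**The concern.** The rule does not yield the quantity it names. An average day of the week contains five parts weekday to two parts weekend day, and adding two values and averaging them treats the two kinds of day as equally common.

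The resulting error is not a constant that drops out of a model. It is proportional to each child's own weekend-minus-weekday difference, so it varies between children and can vary within a child from wave to wave. The planned model separates between-child from within-child variation and estimates change over three waves, so the relative weight of weekday and weekend viewing affects what counts as change in this mediator. It also affects any minutes per day that are reported.

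**Working it through.** **Inputs.** From the article: one weekday value (WD) and one weekend-day value (WE) per child per wave, summed and averaged. From the calendar: 5 weekdays and 2 weekend days. The article gives no means, SDs or correlation for WD and WE, so every value of these below is an assumption. It also prints no screen-time figure that could be reproduced.

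**Formulas.**
- Rule as written: S = (WD + WE)/2.
- Calendar-weighted daily mean: W = (5·WD + 2·WE)/7.
- Difference: S − W = (1/2 − 2/7)·(WE − WD) = (3/14)·(WE − WD) = 0.214·(WE − WD).

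**Weights.** Weekend: 0.500 against 0.286, a ratio of 1.75. Weekday: 0.500 against 0.714, a ratio of 0.70.

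**Error in level, for assumed gaps.**

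| WE − WD | S − W |
|---|---|
| 0 | 0 |
| 0.5 h (30 min) | 30 × 3/14 = 6.4 min |
| 1 h (60 min) | 60 × 3/14 = 12.9 min |
| 2 h (120 min) | 120 × 3/14 = 25.7 min |

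A negative gap gives the same sizes with a minus sign. The relative error also depends on the level:
- WD 90 and WE 120 min: 105 against 98.6 (+6.5%).
- WD 60 and WE 120 min: 90 against 77.1 (+16.7%).
- WD 60 and WE 180 min: 120 against 94.3 (+27.3%).

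**Error in change between waves.** Let one component change by δ and the other stay fixed.
- Weekday only: the rule records δ/2, the true change in the daily mean is 5δ/7, and the ratio is 0.70. The change is under-counted by 30%.
- Weekend only: the rule records δ/2, the true change is 2δ/7, and the ratio is 1.75. The change is over-counted by 75%.
- Both by the same amount: the rule records it correctly.

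**Ranking of children.** Set the weekday SD to 1, the weekend SD to k and their correlation to r. For r = 0.5 and k = 1:
- cov(S, W) = 0.5 + 0.5 × 0.5 = 0.75
- var(S) = 0.25 + 0.25 + 0.5 × 0.5 = 0.75
- var(W) = (25 + 4 + 20 × 0.5)/49 = 39/49 = 0.796
- correlation = 0.75/√(0.75 × 0.796) = 0.971

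Over assumed r from 0.3 to 0.9 and k from 1 to 2, the correlation between the two versions runs from 0.947 to 0.995. The rule therefore distorts the level more than the ordering of children.

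**The case against.** **The sentence may be shorthand.** This is one line in a condensed article, it gives no divisor, and the quantity it names is the right one. The full analysis plan is not shown, and the source cited for the measure may set a scoring convention that cannot be checked here. This stands as a caution: it is not certain that the error will be made. But the article does state a rule, and someone coding from it would write (WD + WE)/2. If weights were intended, the text still needs them.

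**The minute figures concern the wrong quantity.** The objectives do not rest on mean screen time. Screen time enters as a mediator, where associations and change matter, and under the assumed range the two versions correlate at about 0.95 or more. This largely stands. If every child's change came from weekdays alone, the recorded change would simply be 0.70 times the true one. The path into screen time would shrink by that factor, the path out would grow by its inverse, and their product would be unchanged. Distortion beyond scaling needs children who differ in which component changes. The correlation range was worked out for values at one wave, so it does not settle the within-child question.

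**The scope is narrow.** Screen time is one behaviour beside diet, four eating behaviours, physical activity, sedentary time and sleep. It is not the outcome, and the Sample Size Estimation section does not refer to it. This stands.

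**A stronger reading is tempting.** A reader might infer that the error is differential: caregiver employment and pandemic closures shape weekday care, hence the weekday-weekend gap, and are also tied to the stress exposures. The article does not support this as a finding. It records COVID-19-related employment change and employment status, but it connects neither to screen time, does not list child-care attendance among its measures, and reports no weekday or weekend values. Nor can a reader conclude that screen time will be overstated, because that requires weekend viewing to exceed weekday viewing.

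**Conclusion.** The point holds as a minor error in a stated derivation rule. Read plainly, the rule gives weekends 1/2 instead of 2/7 and misses the daily average by 3/14 of the weekend-minus-weekday gap. The weights and the 30% and 75% figures for single-component change follow from the calendar alone. The figures of 6, 13 and 26 minutes rest on assumed gaps with weekend viewing higher. The expectation that between-child mediation paths move little rests on assumed correlations and SD ratios. Differential error by stress exposure is possible, but neither its presence, its sign nor its size can be drawn from the article. Nothing here suggests that the study's main conclusions would be overturned.

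**What to change.** Replace the derivation sentence with an explicit formula: average daily screen time = (5 × weekday value + 2 × weekend-day value)/7, computed identically at baseline, year 1 and year 2. If a weighted mean was always intended, only the wording changes.

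The cost is one line of derivation code. Both values are already collected at each wave, and the Results section says that cleaning and analysis were still under way at publication, so no new data are needed. The change is best made before the structural equation models are fitted. If any model has already been run on the unweighted score, it should be rerun and the two sets of screen-time paths compared.

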### Potential Moderating Variables

Primary caregivers report their child’s sex. Both the primary and secondary caregiver report their education level. Quality of caregiver relationship is assessed for both primary and secondary caregivers using the warmth or affection subscale of the Parenting Acceptance and Rejection Questionnaire [58,71] which measures parents’ feelings of warmth and acceptance (vs rejection) toward their child, a central aspect of relationship quality [72,73] that has been associated with multiple child outcomes [74,75]. Caregivers respond to items including “I say nice things about my children” on a 4-point Likert scale from 1 (almost always true) to 4 (almost never true). After reverse coding relevant items, a total score will be calculated by summing the responses. Both the primary and secondary caregivers completed an abbreviated 30-item version of the Behavior Rating Inventory of Executive Function [76] to assess caregiver self-regulation. A total score will be calculated by summing the responses across the 30 items. Time-varying moderators will be assessed at all 3 time points, whereas time-invariant moderators will only be assessed at baseline.

### Covariates

Primary caregivers report their child’s birth weight, gestational age, duration of breastfeeding, annual and sources of household income, child and caregiver race or ethnicity, and caregiver employment status (full- or part-time). Secondary caregivers report their race or ethnicity and their employment status.

### Retention

The research team has extensive experience in strategies for retention in longitudinal family studies [77-79]. To maximize retention in the Family Stress Study, many of these same strategies are used including (1) regular emails to maintain connection with participants, (2) mailings with tracking to obtain forwarding address information, and (3) financial incentives for assessments.

### Data Analyses

To summarize baseline caregiver and child characteristics for this paper, descriptive statistics were used. Percentages are presented for categorical data. Means and SDs are used for continuous data.

This study’s objectives will be tested using an SEM approach for longitudinal models that combines latent growth models (LGMs) with auto-regressive and cross-lagged paths using a special parameterization that separates the time-invariant (between-individuals) and time-varying (within-individuals) components [80,81]. Before constructing the SEM models, distributions of all the variables, their skewness and kurtosis levels, and their presence of extreme or outlier responses above or below 3 times the IQR will be explored and outliers will either be removed or Winsorized.

An incremental model-building approach similar to the recommended approach by Curran et al [80] will be used to test this study’s objectives. The first component in the model-building approach is the LGM of the trajectories across time for the variables’ chronic stressors (explanatory variable), child cortisol and child behavior (mediator variables), and child adiposity (outcome variable). Each variable has its own trajectory and includes an intercept (I), which refers to a baseline value, and a slope (S), which refers to change over time. Of particular importance is that individual child variation in these I and S parameters will be modeled. If any of these components are found to be not statistically significant, they are removed from the model. Typically, the I means and variances are significantly different from 0, but the S means may or may not depict significant linear change. The second component consists of the auto-regressive associations (ie, T2 regressed on T1, and T3 on T2) capturing the rank-order stability of the variables across the 3 time points (eg, the relationship between cortisol at T1 and T2). The third component typically consists of cross-lagged paths or other hypothesized paths between the variables, accounting for growth factors, and stability factors. In this study, this component will consist of the longitudinal mediation paths (ie, from explanatory variable at T1 to mediator at T2, to outcome at T3). The hypothesized model includes 2 partial mediators of the relation between stressors and child adiposity: child cortisol and behaviors. To test mediation, a direct path from stressors at T1 and child adiposity at T3 is also included. A correlational path between the residualized mediators is also included to model any leftover covariance between them. The fourth component will assess the moderation of the mediated paths. For example, to test the hypothesis that the cortisol mediation may differ across the sex of the children, we can use a multiple groups SEM approach that compares the effect size of mediation across male and female children.

As with any longitudinal study, attrition is expected. Patterns of missing data and potential bias at time 2 and time 3 will be investigated by comparing demographics and variable scores of participants who are missing to those who are not missing at each time point. In addition to noting and acknowledging any bias due to missingness, the SEM modelling procedure uses a maximum likelihood estimator which also provides one of the best ways to estimate the model parameter estimates in the presence of missing data. While there is no guarantee that the data are missing completely at random, in longitudinal designs, data from earlier time points compensates for the missingness at later time points in the estimation procedure.

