**Figure 1 figure1:**
[figure not shown]
Conceptual model for the Family Stress Study: a prospective observational study of biological and behavioral pathways linking stress and
child adiposity in young children.

The variables depicted in Figure 1 will be assessed across 3 time points, measured 1 year apart, which will allow the elucidation of the direction and the relative contributions of the complex biological and behavioral pathways linking chronic stress and adiposity. Study results will help inform interventions to modify these pathways and reduce obesity risk among young children in the post–COVID-19 context. This paper describes the approach, protocol methods, and baseline demographics of the participants enrolled in the Family Stress Study.

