Caregiver depressive symptoms are assessed using the 20-item short-form Centre for Epidemiologic Studies Depression Scale (CES-D) [48-50]. Both the primary and second caregivers respond to statements about the previous week including “everything I did was an effort” and “I felt lonely.” Responses are to be scored as 0 (less than 1 day), 1 (1-2 days), 2 (3-4 days), or 3 (5-7 days) and, after reverse scoring relevant items, a total score out of 30 will be calculated by summing the responses. The standardized Cronbach α for the CES-D was found to be 0.88 for mothers and 0.80 for fathers of young children in the Guelph Family Health Study [51]. Parental depression assessed using CES-D has been found to be associated with obesity risk and obesity-related behaviors in children [51,52].

Children’s negative life events are reported using an abbreviated List of Threatening Experiences [53], an 8-item measure of negative life events, for example, divorce. Primary caregivers report negative events for their child across their lifetime (or for the past year on the follow-up surveys) by answering “yes” or “no” to whether or not their child has encountered various events, such as “divorce or separation of parents” or “severe disease or accidents.” The total score will be determined by summing the number of negative events. This measure has been found to be associated with obesity risk in children [54].

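### Linear-only wave means, with non-significant components removed, let a non-linear change common to all children bias the stress-to-mediator lagged paths when both variables shift

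*Protocol article*

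**What the plan says.** The variables "will be assessed across 3 time points, measured 1 year apart". In the Data Analyses section the model is a latent growth model with autoregressive and cross-lagged paths, using a "special parameterization that separates the time-invariant (between-individuals) and time-varying (within-individuals) components". Each variable has an intercept and "a slope (S), which refers to change over time", and individual variation in both is to be modelled. The only shape named for the mean trajectory is a line: "the S means may or may not depict significant linear change". The stated way of revising the growth part is deletion: "If any of these components are found to be not statistically significant, they are removed from the model". No significance level is given, and no step adds a non-linear term or frees the wave means.

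Mediation is then tested along lagged paths, "from explanatory variable at T1 to mediator at T2, to outcome at T3", with a direct path from stress at T1 to adiposity at T3. The same section names maximum likelihood as the estimator.

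Two other places bear on whether the wave means could bend. The Introduction says: "The COVID-19 pandemic fundamentally disrupted life for families and has been a key source of chronic stress for young children". The Chronic Stress section has the caregiver report the child's negative life events "across their lifetime (or for the past year on the follow-up surveys").

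**The concern.** The lagged paths are meant to show whether children with more stress than others, or more than their own usual level, later change more in cortisol or behaviour. A change shared by every child says nothing about that. It should be absorbed by the wave means.

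With three waves, an intercept and a linear slope leave one mean contrast per variable unfitted: the departure of T2 from the midpoint of T1 and T3. A rise and fall, or a step followed by a plateau, falls on that contrast. If stress and a mediator (or the outcome) both have such a departure, the misfit does not stay in the means. The estimator passes part of it to the covariances that identify the lagged paths.

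The result is either a path that does not exist or, more often for shifts in the same direction, the loss of a real positive one. The Sample Size Estimation section justifies 300 children by the ability to detect these cross-lagged effects, so a loss of power there matters.

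**Working it through.** **Plan's own figure.** The Sample Size Estimation section reports 82-86% for a simulation at 300 children. It cannot be rebuilt, because no path sizes, variances or autoregressions are given, and it does not address the shape of the means. The check below therefore stands on its own.

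**Inputs from the protocol article.** Three waves one year apart; intercept plus linear slope; maximum likelihood; a stress-to-mediator lagged path; 300 children.

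**Assumptions (not in the document).** Total SD 1; between-child share of variance 0.5 (range 0.3-0.7); autoregression 0.3 (range 0.15-0.5); stress-mediator correlation 0.2 between and within children; true lagged path 0; residual covariances equal at T2 and T3; 1-df likelihood-ratio test at 5%. The size of the common shift is also assumed.

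**Mechanism.** With sample means m and covariance S, and model means μ and covariance Σ, the discrepancy is

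F = ln|Σ| + tr(SΣ⁻¹) − ln|S| − p + (m−μ)′Σ⁻¹(m−μ).

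Writing d = m−μ, the last term equals tr(dd′Σ⁻¹). The model is in effect fitted to S + dd′.

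**T2 swing δ in both variables.** The means are (0, δ, 0). The least-squares line is flat at δ/3, leaving residuals (−δ/3, 2δ/3, −δ/3). At δ = 0.3 these are (−0.1, 0.2, −0.1). The product added to the stress-T1 by mediator-T2 covariance is −0.1 × 0.2 = −0.02. The true covariance there is 0.5 × 0.2 + 0.3 × 0.5 × 0.2 = 0.13. The sign is negative for same-direction swings and positive for opposite ones. The fitted slope is already zero, so deleting it changes almost nothing.

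**Step δ, then plateau.** (0, δ, δ) = (0, δ/2, δ) + (0, δ/2, 0). The first part is a line, so with linear means a step of δ acts as a swing of δ/2. A 0.5 SD step is a 0.25 SD swing.

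**Stress only.** The mediator residuals are zero, so every stress-by-mediator product is zero.

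**Results with random intercepts and linear means (300 children, true path 0):**

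| Common shift | Path | Rejection |
|---|---|---|
| 0.1 SD swing, both | -0.012 | 5% |
| 0.2 SD swing, both | -0.047 | 9% |
| 0.3 SD swing, both | -0.098 | 22% |
| 0.3 SD swing, opposite directions | +0.138 | 40% |
| 0.5 SD swing, both | -0.222 | 74% |
| 0.3 SD step, both | -0.027 | 6% |
| 0.5 SD step, same / opposite directions | negative / positive | about 14% / 24% |
| Stress only, any size | 0.000 | 5% |
| Mediator only, 0.5 SD swing | +0.062 | 11% |
| Any of these, wave means free | 0.000 | 5% |

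Over the assumed variance and autoregression ranges, the 0.3 SD same-direction swing gives -0.051 to -0.232 and 11-63% rejection. Letting the residual covariances differ between T2 and T3 lowers the rates but does not remove the bias.

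**Effect of removing the slope mean.** At the 0.3 SD swing the path is -0.098 with the slope kept or removed. A simulation of 400 replicates with the removal rule applied gave -0.097 and 23.3%, the slope being dropped in 94% of replicates. With free wave means it gave 0.001 and 7.2%.

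**Effect of removing the slope variances.** With random slopes retained, rejection falls to about 7-11% (lower again at larger slope variances), partly through a larger standard error. Bias of roughly -0.065 to +0.095 remains. With slope variances of 0.02-0.05, however, the random slopes are detected only about 10-34% of the time. The removal rule would therefore usually return the random-intercept model and the rates in the table.

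**Masking.** With a true path of 0.20, power is 73% with no shift. It is 44-48% under a 0.2 SD swing in both variables, and 16-22% (estimate 0.08-0.10) under 0.3 SD. With free wave means it stays at 73%.

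**The case against.** The strongest reply has five parts.

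1. **Random slopes.** The plan stresses individual variation in slopes, and with random slopes kept most of the false-positive excess goes. This is correct while they are kept. The plan's own removal rule makes that unlikely at modest slope variance, and bias remains in any case.
2. **Growth shape.** The word linear appears once, in a general remark, and a fuller plan may free the slope loadings. That is possible. Still, the article goes beyond silence: it describes a mean structure and a deletion rule, and as written they produce the problem.
3. **Fit checks.** A global fit test would show the misfit; it rejected in 99-100% of simulated replicates with 0.2 or 0.3 SD swings. This stands as a safeguard, but the article states no remedy, and one chosen after seeing the data would be unplanned.
4. **Calendar time.** Recruitment ran from July 2020 to December 2021, so a pandemic swing is not common to all children at a wave. This stands. It shrinks the wave-common part, and free wave means will not remove the rest.
5. **Life events.** The change of recall window affects one of five stress measures and no mediator. This also stands: alone it does not bias the path.

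A reader might infer that deleting a non-significant slope mean is what creates the bias, that the pandemic or the recall change makes it certain, or that the study will tend to report false stress effects. The documents support none of these. A retained linear slope gives nearly the same bias. No size of common change is given for any variable. Same-direction shifts work against the hypothesised positive association. Rejection of one stress-to-mediator path is also not the false-positive rate of the whole mediated effect.

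**Conclusion.** The point holds in a conditional form. As described, the mean structure cannot fit a bend in the wave means, and under maximum likelihood a bend shared by stress and a mediator biases the path between them. At 300 children and the assumed variances, this matters from about 0.2-0.3 SD in both variables: 9-22% rejection for same-direction swings, 40% for opposite swings of 0.3 SD, and 14-24% for a 0.5 SD step. With random slopes kept, rejection is about 7-11% with bias remaining. There is little or no effect at 0.1 SD or when only stress shifts. The likelier harm is lost power for a real positive path.

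Every size rests on assumed variances, autoregressions and shifts, and the document supplies none of these. The setting makes a common non-linear change plausible but does not establish it. The change is worth making because it is nearly free, not because the bias is shown to be present.

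**What to change.** State in the analysis plan that the three wave means of each repeatedly measured variable are estimated freely, without a linear restriction, and are kept whatever their significance. Significance-based removal should not apply to them. The lagged, direct and mediated paths then rest on individual differences around the wave means. The mean linear slope can still be reported descriptively.

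The cost is one more mean parameter per variable than the linear model (three against two), or two more than the model with the slope mean removed (three against one). No new data are needed, and in these calculations no power is lost when there is no common shift. The article reports that analysis was still under way at publication, so the change may still be possible.

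This removes only the part of a pandemic swing that is common to a wave. It does not replace a decision on how assessment date is handled under staggered recruitment.
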